
#### 2.4.3. Concomitant Interventions

This trial will be incompatible with receiving any kind of additional psychological or dietetic treatment. Nevertheless, drugs for controlling blood pressure, diabetes, or cholesterol will be permitted.

### 2.5. Randomization

Participants will be randomly assigned to either the experimental or the comparison group using a 1:1 allocation ratio. Blocked randomization will be used, and a computerized random sequence generator (www.random.org) will determine the sequence of each block. First, the size of the block will be established, after which a member of the research team not involved in the assessment sessions or the delivery of the treatment will write down the allocation sequence of each block on a sheet of paper which will be concealed in an opaque, sealed envelope. At the time of allocation, once participants have provided consent, the research team member in charge of the assessments and delivery of the treatment will open the corresponding envelope to reveal the allocation sequence to assign each participant to the corresponding group.

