### 2.1. Trial Design and Setting

The current trial was designed as a randomized, controlled, nonblinded superiority trial with 2 parallel groups. Randomization will be blocked with a 1:1 allocation. The study will be located in the Faculty of Psychology of the University of the Basque Country (UPV/EHU; Donostia-San Sebastián, Spain).

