### 2.7. Masking

Only the person responsible for collecting anthropometric, cardiovascular and dietetic data will be blinded, since knowledge of the treatment being given to participants could influence the measurement of outcomes. In contrast, the person responsible for the measurement of the other variables will not be blinded due to the fact that self-report instruments will be employed. Similarly, blinding of the psychologists and participants will not be possible. In the case of the participants, from the moment they read the informed consent document, they will inevitably be aware of the existence of the 2 interventions.

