### 2.8. Data Collection and Assessment Plans

For the present trial, the outcomes will be measured at baseline, posttreatment, 6-month follow-up, and 1-year follow-up. Weight, body fat percentage, waist and hip circumference, and blood pressure will also be measured monthly during the intervention period (see Figure 1 for details of the assessment schedule). Self-reported measures will be collected using the *Encuesta Fácil* online platform (www.encuestafacil.com). Assessment sessions will take place in a computer room and a laboratory in the Faculty of Psychology at UPV/EHU, located in Donostia-San Sebastian. Blood samples will be collected by a nurse in each participant’s primary care unit. A nutritionist will be responsible for evaluating anthropometric and dietetic aspects, having been trained specifically for that task. A psychologist will be in charge of conducting the assessment sessions for the other variables evaluated in the study, having also been trained for that purpose. The evaluated outcomes and the properties of the assessment instruments to be used are detailed below.

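### Allocation is concealed by block, not by participant, and the envelope is opened by staff in charge of assessment and treatment, so later assignments in an opened block can be seen early and the stated assessor blinding depends on who the opener is

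*Protocol article*

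**What the plan says.** Section 2.1 of the protocol article describes a non-blinded trial: "Randomization will be blocked with a 1:1 allocation". Section 2.5 gives the mechanics:

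- The block size comes first ("First, the size of the block will be established"), but no value is given.
- The sequence is prepared by "a member of the research team not involved in the assessment sessions or the delivery of the treatment". That person "will write down the allocation sequence of each block on a sheet of paper which will be concealed in an opaque, sealed envelope".
- Opening follows consent and is done by someone else: "the research team member in charge of the assessments and delivery of the treatment will open the corresponding envelope to reveal the allocation sequence". Each participant is then assigned from that sheet.

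Section 2.7 claims blinding for one role: "Only the person responsible for collecting anthropometric, cardiovascular and dietetic data will be blinded". It says openly that the assessor of the other variables is not blinded, because those measures are self-reported. Section 2.8 names the two assessors. "A nutritionist will be responsible for evaluating anthropometric and dietetic aspects", and a psychologist runs the assessment sessions for everything else. In section 2.4.1 a nutritionist delivers the treatment as usual (TAU), which both arms receive, and anthropometric measures are taken at each of those sessions.

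**The concern.** Two things look wrong in what section 2.5 states.

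**Concealment.** The sealed unit is the block. Opening the envelope to assign one person reveals the assignment of everyone still to come in that block. The person who prepares the list is independent, but that independence is given up at the opening step, where it matters most. Staff who know the next assignment can steer or time enrolment, deliberately or not. That creates an opportunity for selection bias, which the ANOVA or ANCOVA in section 2.10 cannot be relied on to remove. The stake is higher than usual because participants and therapists are unblinded and most primary outcomes are self-reported.

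**Blinding.** The opener learns the assignments. Section 2.5 describes that person only as in charge of assessments and treatment delivery, which could fit the assessor whom section 2.7 calls blinded. The data at stake are not only secondary measures. The dietetic data include the 24-hour recalls, which measure eating habits, a primary outcome in section 2.8.2.

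**Working it through.** **Step 1: can the opener influence enrolment?** Section 2.6 places the information sheet and consent form in the first assessment session. The opener is in charge of assessments, so a part in enrolment is likely. Section 2.3.1 says only that a research team member confirms eligibility. It neither names the opener nor excludes them.

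**Step 2: how much is visible early?** The plan gives no figure to reproduce. The inputs are 1:1 permuted blocks (sections 2.1 and 2.5), 110 participants (section 2.3.2), and block size B, which is an assumption.

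(a) Block envelope opened at the block's first participant (an assumption). The other B − 1 assignments are seen before those people are enrolled:

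share = (B − 1)/B.

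(b) Comparator: one sealed envelope per participant, with B known to staff. An assignment is then certain in advance only once one arm's places in the block are used up, that is, in the final run of the same arm:

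expected share = (1/B) × Σ 2·C(B−k, B/2)/C(B, B/2), for k = 1 to B/2.

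For B = 4: (1/4) × (2·3/6 + 2·1/6) = (1/4) × (4/3) = 33%.

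(c) Block envelope opened only after every member of the block has consented: 0% before enrolment.

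| B (assumed) | (a) block envelope, opened at first participant | of 110 | (b) individual envelopes, B known | of 110 |
|---|---|---|---|---|
| 2 | 50% | 55.0 | 50% | 55.0 |
| 4 | 75% | 82.5 | 33% | 36.7 |
| 6 | 83% | 91.7 | 25% | 27.5 |
| 8 | 88% | 96.2 | 20% | 22.0 |
| 12 | 92% | 100.8 | 14% | 15.7 |

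The harm attributable to the block envelope is the difference between (a) and (b): nil at B = 2, about 42 percentage points at B = 4 (75 − 33), and about 77 at B = 12 (91.7 − 14.3). Larger blocks normally make allocation harder to guess, as (b) shows. Under (a) they make it worse.

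**Step 3: who is the opener?** Set section 2.5 beside sections 2.7 and 2.8.

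- *The nutritionist.* This is the only role that the article explicitly gives both assessment duties (section 2.8) and treatment delivery (section 2.4.1), and section 2.9 refers to the nutritionist in the singular. If this person opens the envelope, section 2.7 cannot be true for anthropometric, cardiovascular and dietetic data.
- *The psychologist.* Section 2.7 already declares the assessor of the other variables unblinded. If this person opens the envelope, sections 2.5, 2.7 and 2.8 agree. The article does not say whether the assessing psychologist is one of the two therapists in section 2.4.2.

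Delivering TAU does not by itself unblind the nutritionist, because both arms receive it. Opening the envelope would.

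**The case against.** The strongest reply is that section 2.5 may describe batch allocation. It speaks of participants in the plural having consented before an envelope is opened, and the Mind&Life groups of 12 to 14 (section 2.4.2) make it natural to assemble a cohort and allocate it at once. Nothing would then be disclosed before enrolment, and unopened blocks stay concealed on any reading. This stands as a possibility, and it is why the exposure runs down to 0%. It does not dispose of the point. Section 2.5 does not require the whole block to have consented. Even in a batch, the opener would see the list while placing known people into it, with no order stated.

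A reader might infer that upcoming assignments *are* known to the person who enrols. The article does not support that: the enroller is not identified, and the time of opening relative to the rest of the block is not fixed. A reader might also infer that the assessor blinding is flatly contradicted. That is too strong, since it fails under one reading of the opener and holds under the other.

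It might also be said that allocation could precede baseline assessment, because consent is the only stated condition for opening. That should not be held against the plan: the schedule of events in Figure 1 is not available here and may settle it.

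**Conclusion.** The point holds in a conditional form. As written, section 2.5 conceals blocks rather than individual assignments and hands the opening to staff who assess and treat. Unless the whole block has consented first, later assignments in an opened block become visible to people likely to be involved in enrolment. If envelopes are opened at the first participant, the exposure is about 75% to 92% of assignments for blocks of 4 to 12, against about 33% to 14% with individual envelopes and a known block size. It is 0% with whole-block consent before opening, and there is no excess at a block size of 2. Block size and time of opening are both assumptions. This is an opportunity for selection bias, not evidence that it will occur.

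On blinding, section 2.5 is in tension with sections 2.7 and 2.8 and is not shown to contradict them. The blinding fails if the nutritionist opens the envelope, and that would reach a primary outcome, eating habits.

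**What to change.** - Use one sequentially numbered, opaque, sealed envelope per participant, tied to the ID number that section 2.9 already issues after consent. Alternatively, keep block envelopes but require every member of the block to have consented, with places in the sequence fixed by ID order, before the envelope is opened.
- Have the envelope opened by the team member whom section 2.5 already describes as outside assessment and treatment.
- State that the blinded assessor is not told the assignment, name by role who opens the envelope, and reconcile sections 2.5, 2.7 and 2.8.

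The cost is about 110 envelopes instead of one per block, some minor logistics so that the independent member is available at allocation, and a short change of wording. No new staff are needed, and neither the sample size nor the analysis changes.

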### 2.6. Plan to Promote Participant Adherence or Retention

Given the importance of adherence to treatment and retention in the study, the following strategies will be implemented. In the first assessment session, together with providing the information sheet and informed consent form, researchers will highlight the importance of adhering to the treatment, which will also be mentioned in the first treatment session. In particular, the researchers will emphasize the benefit of attending sessions, doing homework, and practicing mindfulness, as well as recording their daily physical activity, diet, and mindfulness practice in their everyday life. Further, in order to promote adherence to treatment, the interventionists will send a message to all participants to remind them of each TAU appointment and group session with Mind&Life once they are held biweekly. Similarly, in order to favor participant retention, in each dietetic assessment session, all participants will be given oral (and written, if requested) feedback explaining their physical state and overall development (based on anthropometric indicators). Additionally, it is expected that both the interventionists and researchers will be available to be contacted by telephone or email at any time throughout the entire study period. In all cases, attendance and attrition will be recorded with the aim of eventually comparing results based on these rates.

### 2.7. Masking

Only the person responsible for collecting anthropometric, cardiovascular and dietetic data will be blinded, since knowledge of the treatment being given to participants could influence the measurement of outcomes. In contrast, the person responsible for the measurement of the other variables will not be blinded due to the fact that self-report instruments will be employed. Similarly, blinding of the psychologists and participants will not be possible. In the case of the participants, from the moment they read the informed consent document, they will inevitably be aware of the existence of the 2 interventions.

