### 2.9. Data Management

Upon enrollment in the study, demographic information will be entered electronically into an Excel file to which only 2 investigators will have access. Likewise, data collected at baseline, posttreatment, 6-month follow-up, and 1-year follow-up will be accessible to only 1 investigator. Informed consent sheets, questionnaires administered on paper format, blood test results, and data related to anthropometric indicators, blood pressure, and 24-h recalls will be kept in locked cabinets which can only be accessed by the same researcher, although the nutritionist will also be aware of the latter piece of information. The information stored online will be copied onto the hard disk of the project. To ensure confidentiality, pseudonymization will be used, where participants will be provided with an ID number after signing the informed consent form, which will be used for assessments. Data forms and identification information will be stored separately, and once all data have been collected, identification information will be eliminated. Participant data will be stored in a file that will be the responsibility of the University of the Basque Country (UPV/EHU). Participants will be provided with information required to access their personal data utilized in the study, and they will be informed of their rights. Data will be preserved unless the interested individual requests its suppression.

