### 2.10. Data Analysis

Primary, secondary and process-outcomes will be analyzed using the statistical program SPSS version 26.0 for Windows (IBM Corp., Armonk, NY, USA). Taking into account the aims of the study, the effects of the Mind&Life program will be examined by analysis of variance (ANOVA) and/or covariance analysis (ANCOVA), with group as the independent or fixed variable (experimental or control) and all study outcomes as dependent variables. If any difference in relation to a variable exists at baseline, it will be introduced as a covariate in the analyses. Likewise, when making comparisons at follow-up points (6-month and 1-year follow-up), pretreatment–posttreatment changes will also be introduced in the analyses as covariates. To estimate effect sizes, Cohen’s *d* will be calculated where values between 0.2 and 0.4 will indicate small effects; between 0.5 and 0.7, medium effects; and above 0.8, large effects [70]. Additionally, we will use multiple regression in order to predict the variables that best explain changes in the quality-of-life criterion variable. For mediation and moderation analyses, AMOS software will be used. For each test, values of *p* ≤ 0.05 will be considered significant.

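### The masking statement by implication leaves the analyst unmasked while the choice of model stays open; fix the model first, and code the arms for the analysis

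*Protocol article*

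**What the plan says.** **Masking.** Section 2.7 of the protocol article says that "Only the person responsible for collecting anthropometric, cardiovascular and dietetic data will be blinded". It adds that "the person responsible for the measurement of the other variables will not be blinded" and that participants and psychologists cannot be masked. Section 2.1 describes the trial in the same sense: "The current trial was designed as a randomized, controlled, nonblinded superiority trial with 2 parallel groups". No section says who runs the analysis or whether that person sees arm labels.

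**Data access.** Section 2.9 says that "data collected at baseline, posttreatment, 6-month follow-up, and 1-year follow-up will be accessible to only 1 investigator". It provides for pseudonymised ID numbers but does not mention coding of the arms.

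**Model.** Section 2.10 says that "the effects of the Mind&Life program will be examined by analysis of variance (ANOVA) and/or covariance analysis (ANCOVA" with group as the factor. A variable that differs between arms at baseline is to become a covariate, but no threshold and no list of variables to check is given. For the 6-month and 1-year comparisons, the change from pretreatment to posttreatment is a set covariate.

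**Allocation.** Section 2.5 has the sequences written by "a member of the research team not involved in the assessment sessions or the delivery of the treatment".

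**The concern.** Participants and therapists know the arm, and most primary outcomes are questionnaires that participants complete themselves. The analysis is a stage at which masking is still possible at almost no cost, and section 2.7 itself accepts that knowledge of treatment can influence outcome measurement.

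Two features then meet. The masking sentence is worded as a complete list with one entry, and the analyst is not on it. The analysis section leaves two decisions to be made with data in hand: whether to adjust, and what counts as a baseline difference. Someone who makes those decisions knowing which arm is Mind&Life can, without intending to, settle on the version that flatters it. The estimate would then lean in one direction, and a reader of the results could not detect this.

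**Working it through.** The plan gives no figure on this point, so there is none to reproduce. Two effects have to be kept apart: what knowing the arms adds, and what the open model adds.

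**Inputs**
- Recruited per arm: 55, with 20% attrition (section 2.3.2, Sample Size). Evaluable: 55 × 0.8 = 44 per arm.
- Test: two-sided 5% (same section), so 2.5% in each direction.
- Candidate analyses at posttreatment: ANOVA on the post score, or ANCOVA adjusting for the baseline value of that outcome (section 2.10 allows either).
- Correlation ρ between baseline and outcome: not in the document; assumed 0.3 to 0.7.
- True effect: zero. Outcome SD: 1.

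**Step 1. Bias when the arms are known.** The ANOVA and ANCOVA estimates differ by the regression slope times the chance baseline difference between arms. With slope ≈ ρ, that gap is approximately normal with mean 0 and standard deviation ρ√(2/n). Both estimates are unbiased on their own. If the larger one is always reported, the expected value is half the mean absolute gap:

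bias = ½ × ρ × √(2/n) × √(2/π)

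With n = 44: √(2/44) = 0.2132 and √(2/π) = 0.7979, so bias = 0.0851 × ρ.
- ρ = 0.3: 0.026 SD
- ρ = 0.5: 0.043 SD
- ρ = 0.7: 0.060 SD

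Simulation agrees, at about 0.03 to 0.06 SD. Against the planning effect of 0.68, this is roughly 4% (0.026/0.68) to 9% (0.060/0.68).

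**Step 2. Bias when the arms are coded.** An analyst who sees only A and B can pick the smaller p-value but cannot choose a direction. The rule is symmetric in the labels, so the expected bias is about 0.

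**Step 3. False-positive rate.** Simulation of 20,000 null trials per value of ρ, 44 per arm (Monte Carlo standard error near 5%: √(0.05 × 0.95/20,000) ≈ 0.15 percentage points):

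| Rule | ρ = 0.3 | ρ = 0.5 | ρ = 0.7 |
|---|---|---|---|
| Always ANCOVA, two-sided | 4.8% | 4.9% | 5.2% |
| Either test significant, two-sided | 6.3% | 7.1% | 8.4% |
| Either test significant in favour of Mind&Life | 3.3% | 3.5% | 4.1% |
| Adjust only if baseline p < 0.05 (assumed threshold), two-sided | 4.7% | 4.2% | 3.6% |

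**Step 4. Does masking change the error?** A separate run at ρ = 0.5, 0.6 and 0.7 compared the two analysts directly.
- Coded arms, smaller p reported: two-sided 7.4%, 7.6%, 8.2%; in favour of Mind&Life 3.5%, 3.8%, 4.1%.
- Known arms, more favourable test reported: in favour of Mind&Life 3.5%, 3.8%, 4.1%; two-sided 4.7%, 4.8%, 4.9%.

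The favourable error is identical. With known arms, only the errors against Mind&Life shrink (for example 4.7% − 3.5% = 1.2% at ρ = 0.5). That imbalance is the tilt found in step 1.

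**The case against.** The strongest objection is that masking is the wrong target. The rise in false positives belongs to the open model in section 2.10, and step 4 shows that coding the arms would not remove it. Fixing one model would close the choice whether or not anyone is masked. This stands, and it is why the fix puts the model first. What remains for masking is the directional shift in the estimate.

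A second objection is scope. Section 2.7 is written about measurement and delivery, section 2.9 is a confidentiality provision, and how labels reach the analyst is often left to a statistical analysis plan or full protocol, neither of which is shown. A reader might infer that the plan forbids masked analysis, or that the investigator holding the data is a known, unmasked analyst. The document does not say either. What stands against the objection is the restrictive first word of section 2.7: a later plan that masked the analyst would depart from that sentence as written.

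A third objection is that covariates are not freely chosen. Section 2.10 gives a trigger at baseline and sets the follow-up covariate. If the trigger were applied mechanically at an assumed p < 0.05, error would not be inflated (3.6% to 4.7%). This also stands. The part left open is what counts as a difference and which variables are checked.

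**Conclusion.** The point holds in a limited form. By the literal wording of section 2.7 the analyst is unmasked, by inference only, while section 2.10 leaves the choice of ANOVA or ANCOVA and the baseline trigger undefined. An analyst who knew the arms and took the more favourable result would bias the estimate by about 0.03 to 0.06 SD towards Mind&Life, against about zero with coded arms. The rise in favourable false positives from 2.5% to about 3.3% to 4.1% comes from the open model and not from the lack of masking. It would be wrong to infer from it that unmasking alone inflates the error rate.

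These figures assume 44 evaluable per arm, no true effect, a correlation of 0.3 to 0.7, and consistent selection of the better of two analyses. They describe what the wording would permit and are not a prediction of what the team will do. The size is modest; the case for acting rests on the very low cost.

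**What to change.** Amend sections 2.7 and 2.10 together.

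1. **Fix the model.** Name one analysis for every outcome, for example ANCOVA on the baseline value of that outcome, in place of "will be examined by analysis of variance (ANOVA) and/or covariance analysis (ANCOVA" and the undefined baseline trigger. List and date-stamp the covariates before any between-group result is viewed, including results on coded arms.
2. **Code the arms.** State that the analyst works on a data set with arms labelled A and B. Keep attendance, mindfulness logs and telephone-call records in a separate file, because the logs and calls belong only to Mind&Life and would reveal the arm. The team member who writes the allocation sequences (section 2.5) can hold the code, provided that person does not run the analysis.

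The cost is a few sentences and one recoded variable, with no extra staff. The limit is that a large effect may let the analyst guess the arm, so the masking is partial. It complements the fixed model and does not replace it.
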